#### Laboratory assays

Specimens for HPV testing are transported overnight by courier at ambient temperature to the UW Mombasa Laboratory for HPV testing. If storage is necessary prior to courier pickup, the samples are maintained at 4°–25 °C for up to 4 weeks from collection date. To ensure temperature excursions do not occur, the specimen package is placed in a cooler box with ice packs to maintain appropriate temperature during transit. Specimens are not allowed to freeze. The temperature is confirmed by the receiving laboratory.

HPV DNA genotyping is conducted using the Anyplex II HPV28 assay (Seegene, Seoul, South Korea), a multiplexed real-time type-specific PCR assay that simultaneously detects, differentiates, and semi-quantifies 28 HPV genotypes (19 hrHPV types and 9 lrHPV types) [16, 17]. The Mombasa laboratory participates in proficiency studies for HPV DNA detection and typing.

Plasma or serum specimens are shipped to the University of Washington, Seattle, WA, USA, where they are scanned and stored for specialized antibody testing. At the time of testing, specimens are transported to the nearby (2 miles) Fred Hutchinson Cancer Research Center under controlled conditions. HPV antibodies are detected in serum or plasma using a Luminex assay for detecting HPV antibodies. For the subset of women in the B cell studies, peripheral blood mononuclear cells (PBMC) are prepared at the Kisumu Site Laboratory in Kenya and shipped on dry ice directly to the [name] Lab at Fred Hutchinson Cancer Research Center.

#### Plans to promote participant retention and complete follow-up {18b}

Retention activities are proactive. Participants receive text messages or telephone calls reminding them of their upcoming study visits. At study follow-up visits, free comprehensive sexual and reproductive services are offered on site. Outreach is conducted by a study team member to participants who miss visits by text, phone, or in-person visits, with their permission.

The sites’ retention strategies focus on:
Personalized attention: counseling focused on individual adolescent girls and young women, listening, empathy, and proactive management such as linking to appropriate services,High quality standard of clinical care through regular staff training,Comprehensive SRH services,Good customer care with a holistic approach including baby friendly clinics, andParticipant event days to celebrate girls and young women and provide learning opportunities.

## Data management {19}

### Data collection

Completed electronic cases report forms (CRFs) and laboratory forms are submitted to the data analyst at the University of Washington. Data are entered into a study-specific database by trained study staff using the electronic DFnet© software.

The primary mode of data collection for case report forms is electronic, with paper forms as backup in case of internet outages. Data collected on paper CRFs are entered electronically once connectivity is reestablished. The computers used by clinicians and data personnel are password-protected. Source documents such as some laboratory results are in paper format.

### Data quality checks

Data quality control is done on-site. Additional data checks and data cleaning are done by trained data managers at DFnet and UW under the supervision of a senior data manager. Study progress is monitored weekly with either fortnightly, or, at a minimum, monthly quality control measures conducted by the study analyst, based at the University of Washington, with oversight from the senior data manager and study investigators.

### Data management plan

When reviewing, exporting, or managing data, all communications between browser and server are encrypted. Servers are secured by firewalls to prevent unauthorized access. Data is protected from virus threats using anti-virus technology. The study database is backed-up regularly, both on-site and off-site. At the conclusion of the study, the database will be archived in accordance with study site procedures. Data captured on paper forms are stored securely in locked file cabinets.

Site investigators maintain, and store in a secure manner, all study records throughout the study implementation and post implementation. All study clinics have an archival store with limited access and fire safety measures in place. All study records will be retained according to local regulatory guidelines.

## Confidentiality {27}

Site staff conduct all study procedures in private and protect participant privacy and confidentiality to the extent possible. Study-related information is stored securely at the sites. Sites maintain any records that contain names or other personal identifiers, such as locator forms and informed consent forms, separately and securely with limited access. Sites also secure forms, lists, logbooks, appointment books, and any other listings that link participant numbers to identifying information in a separate, locked file area. Laboratory specimens, data collection, and administrative forms are identified only by coded number and are also kept secure, with access limited to study staff. Sites will protect any on-site databases with password access systems.

Participants’ study information will not be released without their written permission, except as necessary for review, monitoring, and/or auditing by the following:
KEMRI Scientific Ethics Research Unit (SERU)Kenya Pharmacy and Poison BoardRepresentatives of the US Federal Government, including the US OHRP, representatives of the US and host government and other local and US regulatory authoritiesStudy management staffSite staffSite and central IRBs/ECsSponsorsContractors working on behalf of the trial management

## Plans for collection, laboratory evaluation, and storage of biological specimens for genetic or molecular analysis in this trial/future use {17}

Specimens collected in this trial are stored for future use. Blood and genitourinary specimens are stored securely at the Thika, Nairobi, and Kisumu sites and at the University of Washington and the Fred Hutchinson Cancer Research Center for future research. These samples may be used for research related to HPV vaccines, HPV, BV, HIV, HIV-related diseases, and STIs. Samples are stored using barcodes that are not personal identifiers. The Scientific and Ethics Review Unit (SERU) in KEMRI, Kenya, has regulatory oversight over the safety and rights of research participants and must approve any future research studies using study data and samples. Participants can decline storage of samples when completing their informed consent or withdraw consent for sample storage up to 5 years after the study conclusion.

## Statistical methods

### Statistical methods for primary and secondary outcomes {20a}

#### General statistical considerations

Descriptive analyses summarizing baseline and follow-up data will be stratified by site and/or country and treatment arm separately. Line, scatter, and box plots will be used, as appropriate, for longitudinal data representations. If loss to follow-up is greater than 10%, baseline characteristics will be described by loss to follow-up status. Missing data will be imputed.

## Cohorts and datasets for primary and supporting analyses

Analyses will be performed on the following populations.

### Intent to treat cohort

The intent to treat (ITT) population includes all enrolled participants

### Modified intent to treat cohort

The modified intent to treat (mITT) cohort is defined as participants who are HPV antibody negative at the enrolment visit and HPV DNA negative from the enrolment visit to (and including) the month 3 visit. Participants who are HPV DNA positive at month 3 are excluded to ensure exclusion of all participants who had incubating infection and were not yet PCR positive.

### Modified intent to treat sensitivity cohort

The mITT Sensitivity cohort differs from the mITT cohort in that participants are only excluded based on the HPV DNA test and not HPV antibody tests. Therefore, the modified intent to treat (mITT) sensitivity cohort is defined as participants who are HPV DNA negative from the enrolment visit to (and including) the month 3 visit. Participants who are HPV DNA positive at month 3 are excluded to ensure exclusion of all participants who were infected at enrolment.

### Extended sensitivity cohort

The extended sensitivity cohort is defined as the analysis cohort for participants who are HPV DNA negative from enrolment to (and including) the month 6 visit. Participants who are HPV DNA positive at month 6 are excluded to ensure exclusion of all participants who were infected at enrolment and for consistency with previous studies [18].

## Primary efficacy analysis

### Objectives

To separately test the efficacy of immediate single-dose bivalent and nonavalent HPV vaccination to prevent incident persistent HPV 16/18 infection compared to delayed nonavalent HPV vaccination for young women age 15–20 years.To test the efficacy of immediate single-dose nonavalent HPV vaccination to prevent incident persistent HPV 16/18/31/33/45/52/58 infection compared to delayed nonavalent HPV vaccination for young women age 15–20 years.

### Outcome

Outcome is as follows: Persistent HPV, defined as vaccine type specific HPV detected at two consecutive time points no less than 4 months apart after month 3 and up to and including 18 months apart (same HPV type at each time point) in the first 18 months post-randomization.

### Cohorts

Cohorts are as follows: mITT cohort, mITT sensitivity cohort, and extended sensitivity cohort.

### Definition of endpoints

The persistent HPV endpoints (16/18 and 16/18/31/33/45/52/58) are defined in participants who experience the outcome defined above as the time from the month 3 visit to first detection of vaccine type specific HPV.

### Analysis approach

The primary analysis will be performed on the mITT Cohort. If the participant does not reach the outcome of persistent oncogenic HPV infection, as defined above, her infection time will be censored at the last negative test date at or before the month 18 visit (time from month 3 visit to last negative test). A Cox proportional hazards (PH) model stratified by site will be used to assess the efficacy of each vaccine arm compared to control. Vaccine efficacy will be expressed as a percent reduction in the incidence rate (i.e., 100 × [1 − (vaccine infection rate/corresponding control infection rate)]). The log rank test stratified by site will be used to calculate the *p* value. Further details for the analysis are available in the statistical analysis plan.

## Secondary efficacy analyses

Immunobridging sub-study:

Sample size calculation: Using the same assumptions as the main study, we anticipate 70% of young, sexually active women in Kenya will be HPV 6/11/16/18/31/33/45/52/58 naïve (as documented by baseline serology and HPV DNA).

Total sample size: Using the same assumptions as the main study, we estimate that 300 women from each arm (300 × 3 = 900 total) would need to be enrolled in the sub-study.

Power: When the sample sizes in the groups are 150 and 300, a two group 0.025 one-sided *t* test will have 91% power to reject the null hypothesis that the test is inferior to the standard in favor of the alternative hypothesis that the treatment is non-inferior, assuming that the expected difference in log means is 0 (i.e., the ratio is 1.0), a non-inferiority margin of log (0.67) and the common standard deviation is 1.2.

Immunobridging analysis:

Bivalent vaccine: The cohort for primary analysis of non-inferiority includes 15–20-year-old women from this trial and 9–14-year-old girls from the Tanzania trial who received single-dose HPV 16/18 vaccination and who were HPV 16/18 DNA negative and HPV 16/18 seronegative at baseline [19].

Nonavalent vaccine: The cohort for primary analysis of non-inferiority includes 15–20-year-old women from this trial and 9–14-year-old girls from the Tanzania trial who received single-dose HPV 6/11/16/18/31/33/45/52/58 vaccination and who were HPV 6/11/16/18/31/33/45/52/58 DNA negative and HPV 6/11/16/18/31/33/45/52/58 seronegative at baseline [19].

For each vaccine group (bivalent and nonavalent), noninferiority of antibody GMTs at 1 month and 24 months after single-dose vaccination will be tested using a 2-sided 95% CI for the ratio of antibody GMTs in 9–14-year-old girls relative to antibody GMTs in 15–20-year-old young women. Noninferiority will be tested for each vaccine type. Noninferiority will be declared if the lower limit of the ratio is above 0.67. The statistical criterion for non-inferiority requires that the lower bound of two-sided 95% confidence interval of GMT ratio (girls vs. young women) be greater than 0.67 for each HPV type. To facilitate robust analysis of immune-bridging and account for the durability of vaccine efficacy, the 24-month analysis will be the primary analysis with the month 1 analysis providing additional information.

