#### Hypotheses

Single-dose bivalent or nonavalent HPV vaccination will prevent 75% of combined incident persistent HPV-16/18 infections among young women who are HPV 16/18 naïve at enrollment*.*Single-dose nonavalent HPV vaccination will prevent 75% of combined incident persistent HPV 16/18/31/33/45/52/58 among young women who are 16/18/31/33/45/52/58 naïve at enrollment.

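### The nonavalent immunobridging cohort requires negativity for all nine types although each type is tested separately; a type-specific cohort would recover a modest amount of precision at almost no cost

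*Protocol article*

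**What the plan says.** The Immunobridging analysis paragraphs, under Secondary efficacy analyses, define one cohort per vaccine. For the nonavalent vaccine, the primary non-inferiority cohort consists of single-dose recipients from this trial (15–20 years) and the Tanzanian trial (9–14 years) "who were HPV 6/11/16/18/31/33/45/52/58 DNA negative and HPV 6/11/16/18/31/33/45/52/58 seronegative at baseline". The sub-study sample-size paragraph anticipates that 70% of women are naive to the same nine types, so the natural reading is that all nine must be negative.

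The test itself is type-specific: "Noninferiority will be tested for each vaccine type", and the lower 95% limit of the girls-to-women GMT ratio must "be greater than 0.67 for each HPV type". No type-specific cohort is described for these tests.

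The efficacy hypotheses define naivety differently. One uses HPV 16/18 only. The other, for the nonavalent vaccine, is set "among young women who are 16/18/31/33/45/52/58 naïve at enrollment". Types 6 and 11 appear in neither.

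**The concern.** Each GMT ratio describes the response to one HPV type. The direct reason for a baseline exclusion is that earlier infection with, or antibody to, that type could change the titre measured after vaccination. Positivity for a different type does not by itself make a participant uninformative. Under the rule as written, one positive result for any of nine types removes her from all nine comparisons.

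The clearest case is a woman positive only for HPV 6 or 11. Her result does not exclude her from either efficacy hypothesis, but she cannot contribute to the titres used to bridge efficacy to younger girls. For HPV 16 and 18 there is also an asymmetry between vaccines: the bivalent bridge asks only for 16/18 naivety, while the nonavalent bridge for the same two types asks for nine-type naivety.

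What is at stake is the width of each type-specific confidence interval, and hence the chance that each lower limit clears 0.67.

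**Working it through.** **Inputs from the protocol article**
- Test: "a two group 0.025 one-sided" t test, expected log difference 0.
- Margin and SD: "a non-inferiority margin of log (0.67) and the common standard deviation is 1.2".
- Group sizes: "When the sample sizes in the groups are 150 and 300". The text does not say which group is the girls.
- Women enrolled in the sub-study: 300 per arm. Naive to all nine types: 70% (both under Secondary efficacy analyses).
- Loss to follow-up: 10% (Sample size, Assumptions).

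**Formula.** Noncentrality = |ln 0.67| / (1.2 × √(1/n₁ + 1/n₂)), with |ln 0.67| = 0.400. Power comes from the noncentral t distribution with n₁ + n₂ − 2 degrees of freedom.

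**1. The plan's own figure.** For 150 and 300, the standard error is 1.2 × √(1/150 + 1/300) = 0.120, the noncentrality is 0.400/0.120 = 3.34, and power is 91.5%. The statement that the test "will have 91% power to reject the null hypothesis" is reproduced.

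**2. The all-nine rule.** 300 × 0.70 = 210 women; with 10% loss, 210 × 0.90 = 189.

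**3. A type-specific rule.** The protocol gives no naive share for a single type, so a range is assumed.
- Lower value 85%: 300 × 0.85 × 0.90 ≈ 230 women.
- Upper value 96%: if the nine types were equally common and independent, 0.70^(1/9) = 0.961, and 300 × 0.961 × 0.90 ≈ 259 women.

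The upper value is close to a ceiling. Each of the 30% non-naive women is positive for at least one type, so the naive share averaged over the nine types cannot exceed 1 − 0.30/9 = 96.7%.

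**4. Power per type, women after 10% loss**

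| Rule | Women | Girls = 150 | Girls = 300 |
|---|---|---|---|
| All nine types negative | 189 | 86.1% | 94.8% |
| Type-specific, 85% naive (assumed) | 230 | 88.7% | 96.7% |
| Type-specific, 96% naive (assumed) | 259 | 90.1% | 97.5% |

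The number of girls is held fixed in each column because the protocol gives no naive share for them. A type-specific rule could only add girls.

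**5. Clustering.** Anyone naive to all nine types is naive to each one, so a type-specific cohort is never smaller. If the non-naive women were positive for every type, the share naive to a single type would also be 70%, and the gain would be zero.

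**The case against.** The restriction is deliberate. The sample-size paragraph plans for 70% naive to the same nine types, the rule applies to women and girls alike, and no passage contradicts it. An all-types-naive cohort is coherent and guards against cross-type antibody. Power per type stays above 85% on the protocol's own assumptions. All of this stands, and it limits the point to a matter of efficiency.

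Two stronger readings are tempting and are not supported:

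- **That the women's GMT is biased because it comes from a less exposed subset.** No passage shows that the excluded women would respond differently. If exposure to other types does not affect a given type's titre, restricting on it does no harm beyond lost numbers. If it does, the restriction has some value for validity. One cannot argue both that the rule distorts the titre and that it gains nothing.
- **That a type-specific cohort would align the bridge with the efficacy population.** It would not do so fully. The seven-type efficacy hypothesis itself requires naivety to all seven types, so a type-specific HPV 16 comparison would admit, for example, a woman positive for HPV 52 whom that hypothesis excludes. The efficacy mITT cohort also excludes women who are DNA positive at month 3, and the bridging cohort uses baseline status only. What a type-specific rule does remove is the exclusion of 6/11-positive women from the high-risk type comparisons. For HPV 16 and 18 it also moves the cohort closer to the 16/18-naive efficacy population.

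A reader might also multiply the loss across nine types. The joint effect depends on the correlation between the types' results, which the protocol does not give, so no joint figure is claimed here.

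**Conclusion.** The point holds as a minor one. The nonavalent bridging rule discards participants who are informative for a given type, and the protocol gives no stated benefit in return. The loss is about 3 to 4 percentage points of power per type (86.1% against 88.7% to 90.1%) if the girls number 150. It is about 2 to 3 points, from a base of 94.8%, if they number 300.

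This rests on the protocol's 70% naive and 10% loss, on an assumed single-type naive share of 85% to 96%, and on little clustering of infections in the same women. With complete clustering the gain is nil. The restriction does not contradict the rest of the plan, and no bias in the bridge has been demonstrated.

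Nor should the stated 91% be called wrong on this account. If 150 refers to evaluable women, the 189 expected under the all-nine rule already exceed it.

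**What to change.** In the nonavalent paragraph of the Immunobridging analysis, define the cohort by type: for each type's GMT ratio, include the women and girls who were DNA-negative and seronegative at baseline for that type. Keep the all-nine-naive cohort as a sensitivity analysis to check for cross-type antibody. In the power statement, say which group is the 150 and which the 300.

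For this trial's women the change costs a sentence or two and no new data: the protocol already provides for enrolment serology on all nine types and type-specific DNA genotyping. The same type-level baseline results are needed for the girls, and applying the present rule already requires them. The downside is that the participant set differs slightly from type to type. The cohort would still not match the seven-type efficacy cohort exactly, because women positive for other types are admitted and the month 3 DNA exclusion is absent. A short statement of those two differences in the plan would be enough.

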## Analysis plan for B cell studies

For the bivalent and nonavalent vaccine vs. the meningococcal vaccine and for the bivalent vs. nonavalent vaccines we will compare (1) the percent of plasmablasts from PBMCs, (2) the percent of plasmablasts from purified B cells, (3) the percent of HPV 16 specific B memory cells, and (4) number of HPV 16 B memory cells per 10^6 live cells. We will use the ANOVA test for pairwise comparison and the ANOVA for more than two groups. Differences with a *p* value of < 0.05 will be considered significant.

## Cost-effectiveness analysis

Cost effectiveness analysis: We will assess cost, cost-effectiveness, and budget impact of single-dose HPV vaccination to support implementation strategies for single-dose HPV vaccination following WHO recommendation in high cervical cancer burden settings.

Overall approach: Using activity-based micro-costing data and outcome data from aim 1, we will define the costs and model the cost-effectiveness of single-dose HPV vaccination for optimized cervical cancer prevention. We will work closely with the Kenyan Ministry of Health to determine the package of evidence necessary for implementation of single-dose HPV vaccination including budget impact and strategies for mass single-dose vaccination and incorporation of HPV vaccination into health services for young women.

Health economic modeling: We will adapt our existing South African HPV transmission model to explicitly include single-dose bivalent and nonavalent HPV vaccination and parameterize a transmission model for the Kenyan HPV transmission and progression to cervical cancer [20].

*Model outcomes*: We will estimate the impact of single-dose bivalent and nonavalent HPV vaccination on the change in (1) cervical cancer incidence, (2) cervical cancer related deaths, and (3) disability-adjusted life years (DALYs). The model simulates the intervention impact and projects the effect on health outcomes over 10 years. For all key inputs and outputs, we will follow standard practices [21], including the guidelines by the Panel of Cost-Effectiveness in Health and Medicine [22]. We will report on all costs using a recommended discount rate of 3% per year, as well as an alternative 5% discount rate and undiscounted inputs.

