Kenya’s national immunization program, launched in October 2019, offers two doses of the HPV vaccine to 9–10-year-old girls. Further, the Global Alliance for Vaccines and Immunization (GAVI) endorses multi-age cohort vaccination to age 14 years [7]. A gap exists in prevention strategies for young women age 15–20 years, for whom three doses of the HPV vaccine is currently recommended, and the age at which HPV acquisition is highest. Preliminary observation evidence suggests that efficacy of single-dose of HPV vaccination is equivalent to two or three doses [8–12]. Addressing this evidence gap on the efficacy and durability of single-dose HPV vaccine among young women in Africa, particularly as a multi-age cohort vaccination strategy for women age 15–20 years, would simplify the costs of logistics of effective prevention for this priority population. Importantly, the multi-age cohort approach would in the short term provide vaccine protection to adolescents and girls who are not eligible for routine vaccination.

Demonstration projects support the feasibility of high coverage of single-dose HPV vaccination in Kenya. Between 2013 and 2015 and 2016–2018, demonstration projects of the quadrivalent HPV 16/18/6/11 vaccine offered to girls age 9–10 years in a school-based setting achieved > 85% coverage of the first dose with lower coverage of subsequent doses; 64% uptake of the second dose and 39% of the third doses [13, 14]. Furthermore, the current national single-cohort (9- and 10-year-old girls) HPV vaccination program is clinic based and coverage has been lower and affected by the COVID-19 pandemic. The key barriers for transitioning from a single-cohort immunization program to a multi-cohort program are the total costs and logistics associated with the two or three dose vaccine schedules.

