#### Hypotheses

Antibody responses to vaccine-type HPV after receiving a single-dose of bivalent or nonavalent HPV vaccine will be noninferior in 9–14-year-old girls and adolescents compared to 15-20-year-old adolescents and young women.Single-dose bivalent and nonavalent HPV vaccination will be cost-effective per cervical cancer case averted*.*Single-dose HPV vaccination will induce potent memory with B cells producing neutralizing antibodies.Single-dose bivalent or nonavalent HPV vaccination will prevent 75% of combined incident persistent vaccine-type HPV infections among young women who are vaccine-type HPV naïve at enrollment, month 3, and month 6*.*

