## Discussion

This randomized, double-blind, controlled trial will provide data on single-dose HPV vaccine efficacy among adolescent girls and young women age 15–20 years. While observational evidence supports the efficacy of single-dose HPV vaccination [8, 10, 12], this study aims to provide estimates of efficacy to guide public health policy. Further, observational evidence supports multi-age cohort vaccination, up to age 26 years in high-income countries, as a key driver to prevent moderate and severe precancerous lesions over the shortest time period [6]. This strategy of multi-age cohort vaccination has been limited in low-and-middle-income countries by the high cost of the HPV vaccines, the limited supply, and the recommendation for three doses among persons older than 15 years. The KEN SHE Study aims to close that gap in evidence.

The final results of the KEN SHE study are expected in early 2023 and the primary results in Q1 2022. Other trials evaluating single-dose protection are ongoing in Costa Rica (the ESCUDDO trial; NCT03180034), the Gambia (the HANDS trial; NCT03832049), and Tanzania (the DoRIS trial; NCT02834637), with results available at the end of 2021 or later [9, 19]. These trials are all complementary, examining single-dose HPV vaccination for girls, adolescents, and young women age 4–20 years and address different scientific and programmatic questions. In addition to comparing efficacy between study groups, antibody results from A Dose Reduction Immunobridging and Safety Study of Two HPV Vaccines in Tanzanian Girls (DoRIS) Study will be used to immunobridge to the antibody results to the KEN SHE Study (by demonstrating non-inferior antibody levels) enabling extension of the single-dose approach down to girls age 9–14 years [19].

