The KEN SHE Study data will contribute to the Global Strategy towards Eliminating Cervical Cancer as a public health problem led by the World Health Organization (WHO) [27]. Cervical cancer is the 4th most common cancer among women globally, and, the 2nd most frequent in sub-Saharan Africa (SSA), mostly affecting women between ages 30–49 years, and the leading cause of new cancer deaths in SSA [28, 29]. Cervical cancer is an almost entirely preventable cancer with HPV vaccine and the most curable form of human cancer with early detection and treatment. In August 2020, the WHO adopted the Global Strategy to eliminate cervical cancer by scaling up prevention through HPV vaccination—with the global target to reach 90% coverage of HPV vaccination by 2030, 70% coverage of screening and treatment of pre-cancerous lesions, and 90% coverage of management of invasive cervical cancer [27]. However, the estimated global coverage among 9–14-year-old girls for HPV vaccination is 40% with only 8–9% of 10–20 year olds vaccinated [30]. Further, HPV vaccine supply is constrained [7] and SAGE has called for options to optimally allocate existing HPV vaccine supply. Effective single-dose HPV vaccination would facilitate rapid scale up of vaccination worldwide or, in the absence of public health benefit, redouble efforts to ensure adequate supply and implementation of a two- or three-dose vaccination strategy to meet the goal of cervical cancer elimination.

The trial has several strengths including the randomized controlled blinded design, testing two vaccine types, and testing vaccine efficacy over a short time frame to support policy decisions. Further, the secondary objectives will evaluate immunobridging to younger trial participants, assess central memory for vaccine durability, and estimate the population-level impact on cervical cancer incidence and cost-effectiveness, building on the primary study results. A potential limitation of the study is not recruiting participants prior to sexual debut which may limit the number of HPV naïve participants eligible for assessment of vaccine efficacy.

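### The 10-year horizon of the cost-effectiveness model stops before most of the vaccinated cohorts' own cervical cancers would occur, so it cannot adequately test cost per cancer case averted

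*Protocol article*

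**What the plan says.** The Cost-effectiveness analysis section adapts an existing HPV transmission model to Kenya and names three outcomes: change in cervical cancer incidence, in deaths from it, and in DALYs. It then fixes the horizon: "The model simulates the intervention impact and projects the effect on health outcomes over 10 years". Costs are to be reported at 3% per year, at 5% and undiscounted. Budget impact is listed as a separate aim. The article gives no longer horizon and no sensitivity analysis on the horizon.

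The matching hypothesis under Secondary objectives is that single-dose vaccination "will be cost-effective per cervical cancer case averted". The Discussion paragraph of the Abstract says the secondary aims will assess health benefits and cost over the long term.

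On ages, the Discussion describes cervical cancer as "mostly affecting women between ages 30–49 years". The Background presents single-dose vaccination "particularly as a multi-age cohort vaccination strategy for women age 15–20 years". The Discussion also looks to immunobridging as "enabling extension of the single-dose approach down to girls age 9–14 years".

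**The concern.** The horizon and the outcomes do not fit together. The outcomes are late events, and on the article's own account they arise mostly between 30 and 49. The women to be vaccinated are 15–20. A model that stops after ten years counts the vaccination given to a cohort at its start but follows that cohort only to the lower edge of the age range in which the disease mostly occurs.

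The quantity to be tested is cost per cancer case averted. If most averted cases lie beyond the horizon, the ratio reflects where the model was cut off more than what the vaccine does. Varying the discount rate between 0% and 5% also says little about long-term benefit when only ten years are modelled. The section says the work feeds the evidence package for the Kenyan Ministry of Health, so the figure could bear on a policy decision.

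**Working it through.** The 10 years is a choice, not a derived figure, so there is nothing to reproduce. The check is whether it reaches the ages at which the outcomes occur.

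**Step 1. Age at the end of the horizon** = age at vaccination + 10, counting from vaccination. The comparison range is 30–49 (Discussion).

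| Age at vaccination | Age at end | Years needed to reach 30 | Years needed to reach 49 |
|---|---|---|---|
| 15–20 (trial population) | 25–30 | 10–15 | 29–34 |
| 9–14 (immunobridging target, if modelled) | 19–24 | 16–21 | 35–40 |

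Only women vaccinated at 20 touch the lower edge of the range. If the model vaccinates successive cohorts over the ten years, the later ones are followed for less than ten.

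**Step 2. Share of a cohort's own cancers that falls inside the horizon.** The article gives no age-specific incidence, so the age distributions below are assumptions. Cancers are spread evenly within ages 20–29, 30–49 and 50–74. Single-year ages at vaccination are weighted equally and taken at mid-year (15.5 to 20.5). Competing mortality is ignored. With d(age) the assumed density and r the discount rate applied to cases:

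share = sum over t < 10 of d(a+t)/(1+r)^t, divided by the same sum over all t, averaged over the ages a.

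*All cancers at 30–49, undiscounted.* Only women aged 20.5 contribute. They reach 30.5, so 0.5 of 20 years = 2.5%. Averaged over six ages: 2.5%/6 = 0.4%.

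*10% at 20–29, 60% at 30–49, 30% at 50–74, undiscounted.* Ages 15.5 to 19.5 spend 5.5, 6.5, 7.5, 8.5 and 9.5 years of the horizon in the 20–29 band, at 1% of cancers per year: 5.5%, 6.5%, 7.5%, 8.5%, 9.5%. Age 20.5 gives 9.5% + 0.5 × 60%/20 = 11.0%, divided by the 99.5% of cancers still ahead = 11.1%. The mean is 48.6%/6 = 8.1%.

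Percentage captured in 10 years, at discount rates 0% / 3% / 5%:

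| Assumed split 20–29 / 30–49 / 50–74 | Vaccinated at 15–20 | Vaccinated at 9–14 |
|---|---|---|
| 0 / 100 / 0 | 0.4 / 0.5 / 0.6 | 0 / 0 / 0 |
| 2 / 60 / 38 | 1.8 / 3.4 / 4.8 | 0.4 / 0.9 / 1.3 |
| 5 / 60 / 35 | 4.2 / 7.6 / 10.5 | 1.0 / 2.1 / 3.0 |
| 10 / 60 / 30 | 8.1 / 14.0 / 18.7 | 2.1 / 3.9 / 5.4 |

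**Step 3. A longer horizon.** Under the three splits with 60% at 30–49, 40 years captures about 74–80% of the 15–20 cohort's cancers undiscounted, and about 86–90% at 3%. Forty years is therefore a large improvement but still not complete.

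The calculation covers cancers in the vaccinated women. It treats their timing as the timing of averted cancers; deaths and DALYs were not calculated separately.

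**The case against.** Several points on the other side have weight.

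- **Comparator.** A reader might infer that the short horizon biases the result strongly against vaccination. That requires a no-vaccination comparator, and the section names none. The Background says Kenya's programme "offers two doses of the HPV vaccine to 9–10-year-old girls" and describes single-dose vaccination as a replacement for multi-dose schedules. Against a multi-dose schedule, a short horizon would count the immediate saving and leave out any later loss of protection, which could favour the single dose. This objection stands: the direction is not settled.
- **Size.** A reader might also infer that the cases averted within ten years are close to zero. The Discussion says that the disease affects this age range mostly, not exclusively, and with 10% of cancers before age 30 the share reaches 8.1% undiscounted and 18.7% at 5%. That most is missed is supported under the assumptions shown; that almost none is counted is not.
- **Indirect effects.** A transmission model can credit protection to women who are not vaccinated, including older women. That is true and unquantified, so no statement about the total benefit can be exact. It does not restore the vaccinated cohorts' own later benefit.
- **Modelled population.** The section does not say that girls aged 9–14 are modelled, or whether one cohort or a continuing programme is vaccinated. The 9–14 figures are therefore conditional, and it cannot be assumed that all vaccination cost falls early.
- **Condensed text.** The section refers to standard practices and guidelines, and a fuller model plan may exist. A general reference does not override a horizon stated outright for health outcomes.

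**Conclusion.** The concern holds in this form: the stated 10-year projection does not reach the ages at which the article says cervical cancer mostly occurs, so most of the averted cancers, deaths and DALYs in the vaccinated cohorts lie outside it. For women vaccinated at 15–20, the horizon captures about 0.4–8% of their cancers undiscounted and up to about 19% at 5%, if 0–10% of cancers occur before age 30. These shares rest on assumed age distributions and exclude indirect protection.

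The 10-year result cannot adequately test cost-effectiveness per case averted or describe long-term benefit. Against no vaccination it would understate the benefit; against a multi-dose schedule the direction could differ. This is a should-fix on a secondary objective. The primary efficacy analysis, the sample size and the safety monitoring are not affected.

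**What to change.** In the Cost-effectiveness analysis section:

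1. Set the base-case horizon for both costs and health outcomes to the lifetime of the vaccinated cohorts. The minimum is until the youngest modelled cohort passes 49. By the ages above, reaching 49 takes 29–34 years for women vaccinated at 15–20 and 35–40 years for girls vaccinated at 9–14, so about 30–40 years depending on who is modelled.
2. Apply the stated 3%, 5% and 0% rates to health outcomes as well as costs. The present sentence mentions costs only.
3. Keep 10 years for the budget-impact analysis and report the 10-year health result as a scenario.
4. Name the comparator and the ages vaccinated in the model, so that the direction of any horizon effect can be judged.

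The cost is a longer run of a model already being adapted and a few sentences of text. No participant procedure or data collection changes. The downside is greater reliance on assumptions about duration of protection, since trial follow-up for efficacy ends at 36 months. The article describes no scenarios for waning protection in the model, so sensitivity analyses varying its duration should be specified with the longer horizon.
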